### Study setting and recruitment

Participants will be recruited to the trial from St. Erik Eye Hospital in Stockholm as the national management of uveal melanoma patients is centralized to this institution only. The St. Erik Ophthalmic Pathology Laboratory receives most of the eyes with uveal melanoma that have been enucleated throughout the country, meaning that patients will be eligible for the trial regardless of where in Sweden they reside. If the patient is found to meet inclusion and exclusion criteria, they will be contacted via telephone and given information regarding the trial. If the potential participant is interested in taking part in the trial, they will be sent a written consent form and be contacted by a research team member via a service that allows for both video and audio contact, where the potential participant will be able to confirm their identity, ask any questions they may have regarding the trial, and receive additional information. If they wish to participate, they will be asked to sign the consent form (two copies) during the video call and send both of the signed copies in a prepaid envelope to the research team. Once the signed consent form is received by the research team, the participant will be randomized to either the melatonin or the standard treatment group (control group).

As the effectiveness of melatonin will be evaluated in real-life, routine practice conditions, this is considered a pragmatic clinical trial. The study is de-centralized with patients residing in all parts of Sweden eligible, with the drug being delivered to their home address, and with radiological examinations being performed at their home hospitals. Recruitment, randomization, drug prescription, study administration, and follow-up are, however, centralized to St. Erik Eye Hospital.

In contrast to many other western countries, melatonin has not been sold over the counter in Sweden. Since 2020, 3-mg tablets have been sold in packs of 10, at a significant cost to patients. Further, the investigators will be able to detect if trial participants are prescribed melatonin outside the trial through a nationwide digitalized medical journal system.

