### Follow-up

The subjects will take their medication (tablets) at home and confirm that they have received each package of melatonin sent to them. They will, 1 month following recruitment, be contacted via telephone and asked about their compliance to the treatment. The participants will then continue to be contacted via telephone every 6 months throughout the trial period and asked questions about compliance, adverse events (AE), and serious adverse events (SAE). After the termination of the trial, the subjects will continue their yearly control visits at St. Erik Eye Hospital, or at their local ophthalmology clinic, for the remainder of their lives, as all uveal melanoma patients do.

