### Sample size

Our power calculations will be based on the following:A previously calculated metastasis incidence of 60% 5 years following diagnosis for individuals not taking melatonin (participants in the control group). This is a relevant calculation considering the high-risk population recruited based on our inclusion criteria [46–49].An earlier study which included study participants with surgically removed lymph node metastases of malignant melanoma which showed that 31% (5 of 16 participants) of those treated with 20 mg of evening melatonin developed distant metastases compared to 71% (10 of 14 participants) of those not treated with melatonin [8].

Based on this previous research, the following assumptions are made:The number of participants in the melatonin group which will have developed distant metastases after 5 years: 30%The number of participants in the control group which will have developed distant metastases after 5 years: 60%.Alpha: 0.05Beta: 0.2Power: 80%Results: 42 participants must be included in each group, i.e., both the melatonin and the control group, in order to achieve statistical significance (Table 3). To obtain a safety margin in case some participants withdraw from the trial, we will strive after a group population of 50 participants per group.

**Table 3 Tab3:** Power calculation

**Melatonin, *****n***** = **	42
**Control, ***n*** = **	42
**Incidence, melatonin group**	30%
**Incidence, control group**	60%
**Alpha**	0.05
**Beta**	0.2
**Power**	0.8

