### Statistical analysis

We will be analyzing our data according to “intention to treat” where all participants randomized to either the melatonin or control group are included in the said group even if some terminate their participation in the trial or are excluded from the trial later on. We will at the same time analyze our data “per protocol” where the participants who terminate their participation during the trial or are noncompliant to melatonin treatment are excluded from the analysis.

To answer our primary and secondary objectives, we will use both the chi-square test and the Log-rank test of cumulative survival with associated 95% confidence intervals and *p*-values. Relative risk will be calculated as the probability of metastasis in the melatonin group divided by the risk of metastasis in the control group.

*P* values less than 0.05 will be considered significant, and all tests will be double-tailed, or two-sided.The Shapiro–Wilk test will be used to confirm if our continuous data is normally distributed.A Student’s *t*-test will be used to compare the differences in normally distributed continuous data within the melatonin and control groups, respectively. Data found not to be normally distributed data will be compared using the Mann–Whitney *U*-test.In order to compare the risk of death and metastasis between the melatonin and control group, we will also use a Cox Regression, adjusted for covariates such as tumor size, T category, cell type, presence of extra scleral growth, presence of extracellular matrix patterns, and BAP-1 expression.

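### The only stated check for melatonin taken outside the trial covers prescriptions, and the per-protocol rule does not address controls who take it

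*Protocol article*

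**What the plan says.** The Study setting and recruitment section of the protocol article deals with melatonin from outside the trial in three steps. It says melatonin has not been sold over the counter in Sweden. It then says "Since 2020, 3-mg tablets have been sold in packs of 10, at a significant cost to patients". Finally it says "the investigators will be able to detect if trial participants are prescribed melatonin outside the trial through a nationwide digitalized medical journal system".

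Under Follow-up, subjects are telephoned at 1 month and "asked about their compliance to the treatment". Six-monthly calls then cover compliance, AE and SAE. Tables 1 and 2 list the compliance item as compliance with the prescription. Table 2 lists current medication at screening only.

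Under Statistical analysis, intention-to-treat keeps everyone in the randomized group. In the per-protocol analysis, participants who terminate participation or are "noncompliant to melatonin treatment are excluded from the analysis".

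Under Sample size, the control rate is "A previously calculated metastasis incidence of 60% 5 years following diagnosis for individuals not taking melatonin (participants in the control group"). The increase from 42 to 50 per arm is a margin for withdrawal.

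**The concern.** Participants know their allocation, are selected for high risk, have been told about melatonin during consent, and are followed for 5 years. Some controls may therefore obtain it themselves. A record of prescriptions does not show tablets bought in a shop, and a question about compliance with a study prescription has no clear meaning for a control.

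The per-protocol rule is one-sided. It removes melatonin-arm participants who do not take the drug but does not name controls who do. The analysis meant to reflect actual exposure would keep exposed controls as unexposed.

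If melatonin works, use by controls moves the relative risk towards 1 and lowers power. If that use is not recorded as it happens, it cannot be reliably reconstructed after 5 years, and a null result becomes harder to read.

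**Working it through.** **Inputs from the protocol article**
- Melatonin-arm risk at 5 years 30%, control risk 60%, alpha 0.05, power 80%, 42 per arm needed, 50 per arm planned (Sample size and Table 3).
- Two-sided tests and a chi-square test (Statistical analysis).
- Tablets of 3 mg in packs of 10 (Study setting and recruitment); trial dose 20 mg nightly.

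**The plan's own figure.** With pooled variance and no continuity correction,

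n = [1.960·√(2·0.45·0.55) + 0.842·√(0.6·0.4 + 0.3·0.7)]² / 0.30² = 41.97, so 42 per arm. The stated figure reproduces.

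**Assumptions, since the documents give no figure**
- f = share of controls who take melatonin.
- e = share of the full trial effect that such use delivers. Full effect (e = 1) is an upper bound.

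**Formula.** Control risk = 0.60 − 0.30·e·f, with the melatonin-arm risk held at 0.30. Power is the exact binomial probability that the two-sided Pearson chi-square test rejects at 0.05, with 50 per arm analysed and no melatonin-arm stopping. With no control use it is 87.6%.

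| Control use f | Full effect: control risk, RR, power | Half effect: control risk, power | Quarter effect: control risk, power |
|---|---|---|---|
| 5% | 58.5%, 0.51, 84.1% | 59.25%, 85.9% | 59.6%, 86.8% |
| 10% | 57.0%, 0.53, 80.0% | 58.5%, 84.1% | 59.25%, 85.9% |
| 20% | 54.0%, 0.56, 70.2% | 57.0%, 80.0% | 58.5%, 84.1% |

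**Cross-check.** The normal approximation at 50 per arm gives 86.6% with no use, and 82.9%, 78.6% and 68.6% at 5%, 10% and 20% full-effect use. On that method power drops below 80% at about 8.5% full-effect use.

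**If withdrawals use up the margin.** At 42 per arm, 5% full-effect use gives an exact power of 79%.

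**How feasible is full-dose use from bought tablets?** 20/3 = 6.7, so about 7 tablets a night. A pack of 10 lasts 10/7 = 1.4 nights. Five years would take 5 × 365.25 × 7/10 ≈ 1,280 packs. Sustained use at the trial dose by this route is unlikely. Lower-dose use is feasible, but the documents give no effect for it, which is why half and quarter effect are shown.

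**The case against.** The case on the other side has weight.

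- **The protocol does not overclaim.** A reader might infer that it says it can detect any outside use. It does not: the sentence is limited to prescribed melatonin and is correct as it stands.
- **Cost and pack size are offered as the barrier to bought melatonin**, with the record check as an addition. The arithmetic supports this for full-dose use.
- **The two sales sentences** can be read as history followed by a recent, limited change. The wording is clumsy, not a serious contradiction.
- **Control use is not necessarily invisible.** Participants are telephoned every 6 months and the CRF is not shown. The article condenses a fuller protocol that may hold the question.
- **Dilution is not established.** The documents give no rate of control use. At half effect even 20% use leaves 80% power.
- **A null result would not be uninterpretable.** Trial design plans a comparison of controls with earlier cohorts, a partial check on heavy use.
- **Intention-to-treat in a trial described as pragmatic includes real-life use.** Recording that use would not alter the primary relative risk.

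All of this limits the point. What remains is what the article does state: a check on one of two routes, calls described in terms of compliance and adverse events, and a per-protocol rule that names only one direction of departure from allocation. That rule is a stated method, not a detail left to another document.

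**Conclusion.** The point holds as a gap in stated monitoring and in the per-protocol definition. It is not evidence that the primary comparison is diluted.

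Its size depends on an unknown rate and an unknown effect of outside use. At 50 per arm, 5% to 20% control use lowers power from 88% to between 84% and 70% at full effect, between 86% and 80% at half effect, and between 87% and 84% at quarter effect. The full-effect figures are an upper bound, given cost and pack size. All of them assume the protocol's 30% and 60% risks, no withdrawals, and no one in the melatonin arm stopping; stopping in that arm is a separate adherence question.

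The main benefit of acting is interpretive: a null result could be read against a known level of control-arm use. Because the change is cheap and the data must be collected as the trial runs, it is worth making.

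**What to change.** 1. At the existing 1-month and 6-monthly calls, ask both arms about any melatonin from outside the trial (prescribed or bought, amount, how often) and enter the answer in the CRF.
2. Define per-protocol for both arms, so that controls with sustained melatonin use are handled by the same rule as melatonin-arm non-compliers. Fix what counts as sustained before the data are analysed.
3. Report control-arm use beside the primary intention-to-treat result, which stays as planned.
4. Reword the two sales sentences in Study setting and recruitment so that they agree. The sentence on the record system needs no correction, since it already speaks of prescriptions only.

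Cost: one CRF item at calls that already take place, and a sentence or two in the analysis section. Downside: asking may remind controls that melatonin can be bought.

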### Eligibility criteria

#### Inclusion criteria

Participants must be 18 years or older.Participants must give written consent for participation in the trial.Participants must be clinically or histopathologically diagnosed with malignant melanoma originating from the choroid and/or the ciliary body.If the patient has already received treatment with melatonin for another reason, they have had a wash-out period where no melatonin was taken for a least 2 weeks prior to randomization.

In addition to meeting these three criteria, at least one of the following criteria (5–11) must be met as well:5.Participant’s tumor is categorized as a size of T3d or higher, corresponding to stage IIIB or higher (according to AJCC TNM version 8) [36].6.Participant’s tumor is of a size category “large” according to modified COMS criteria (largest basal diameter > 16 mm or thickness > 8 mm) [22].7.Participant’s tumor is of a size category of T2a or higher prior to brachytherapy and has since recurred after brachytherapy [36].8.Participant’s tumor is composed of an epithelial cell type (> 5 epithelial cells/hpf and > 90% epithelial cells in total).9.Participant’s tumor has a low immunohistochemical expression of the BAP-1 protein [37–41].10.Participant’s tumor has 9 or more mitoses per 40 hpf.11.Participant has via another published and validated prognostic test been found to have a risk of 60% or higher for developing metastases after 5 years, for example, “Gene expression class 2,” “TCGA group D,” measurements of protein levels in serum, or similar [3, 42, 43].

#### Exclusion criteria

Participant is oversensitive to melatonin or any of the tablets’ contents.Participant has metastases detectable with radiological examinations or other methods at the time of recruitment (note that the development of metastases later on during the course of the trial does not disqualify a participant).Participant is unable to provide consent.Participant has compromised liver function, for example due to liver cirrhosis or hepatitis.Participant is pregnant, or a woman of child-bearing potential, WOCBP. Any woman between menarche and menopause is considered to have child-bearing potential, if not permanently sterile through hysterectomy, bilateral salpingectomy, or bilateral oophorectomy. Menopause is defined as absence of menstruation for ≥12 months without other explanation.Participant is breastfeeding or wishes to breastfeed before the planned completion of melatonin treatment. Women admitted to the trial who begin breastfeeding during the course of the trial before the studies completion will be withdrawn from the study.Participant has epilepsy.Participant is treated, for more than 4 weeks, with CYP1A2-inhibitors fluvoxamine, quinolones, verapamil, or cimetidine; with combined hormonal contraception (containing ethinyl estradiol and progestogen); with hormonal substitution therapy; with 5-methoxypsoralen or 8-methoxypsoralen; or with cimetidine. If the participant, after being included in the trial, starts a lasting treatment (more than 4 weeks) with one of the previously mentioned substances, the participant does not need to cease participation in the trial but instead can refrain from taking melatonin during their treatment with these substances and then resume their melatonin treatment with the ordinary, daily dose of 20 mg at 10 pm.Participant was diagnosed with primary uveal melanoma more than 12 months prior to the assessment of eligibility.

### Informed consent

A research member will obtain informed consent from the trial participants. In Sweden, informed consent must be collected by a licensed physician. The informed consent form will be sent to the participant via post which the participant will sign if they wish to participate in the trial and send back to the research team who will also sign it and send a copy back to the participant. The participant will then be randomized to either the melatonin group or the control group. Participants will be informed about their right to withdraw from the trial at any time without a need for an explanation. Participants will be asked to consent to monitors, inspectors, research members, and regulatory authorities having access to their data that is relevant to the trial. This trial does not involve collecting biological specimens for storage.

### Interventions

#### Randomization and allocation

The randomization takes place when the participant has sent their signed informed consent form to the research team, agreeing to be a part of this clinical trial. Fifty sheets of paper labeled “melatonin” and 50 sheets of paper labeled “control” will be preserved in a total of 100 sealed, identical envelopes, mixed in one box. When written informed consent is received from a participant, we will randomly choose one of these envelopes and open it. The content will then determine the randomization of the patient, i.e., melatonin or control. When the process of randomization is complete, the participant will be informed of the outcome. If they have been randomized to the melatonin group, they will receive a prescription for melatonin and an order will be placed for 15 containers of melatonin tablets (corresponding to 1 year of consumption) each year during the 5-year period. The participating research staff as well as the participants will therefore be aware of their randomization outcome, either to treatment with melatonin or to composing the control group.

#### Blinding

This trial is not blinded. The study design for this clinical trial is open-label, where blinding will only occur during data analysis by outcome assessors. Therefore, a procedure for unblinding is not necessary.

#### Intervention

Participants will be equally randomized into two groups: the melatonin group (treated with 20-mg melatonin each night for 5 years) or the control group (no intervention). When a patient is recruited and randomized to the melatonin group, blood samples will be ordered by a licensed physician regarding creatinine, electrolytes (sodium, potassium), and alanine transaminase (ALAT). This blood test will be repeated after 2 and 4 years (Fig. 1 and Tables 1 and 2).

**Fig. 1 Fig1:**
[figure not shown]
CONSORT diagram describing study design

**Table 1 Tab1:** Study design

Time	Event in clinical routine	Other events for trial subjects
At diagnosis	Clinical examination of the eye. Radiological examination of the thorax and abdomen. Primary treatment^a^	Provide information about the trial. Screen participant for inclusion and exclusion criteria Obtain written consent. Give medication instructions. Order blood tests to measure kidney function, electrolytes, and liver function. Prescribe melatonin 20 mg every night for 5 years
1 month	A	Ask about AE and SAE, and about prescription compliance
6 months	B	Ask about AE and SAE, and about prescription compliance
1 year	A + B	Ask about AE and SAE, and about prescription compliance
1.5 years	B	Ask about AE and SAE, and about prescription compliance
2 years	A + B	Ask about AE and SAE, and about prescription compliance. Ordering blood tests to measure kidney function, electrolytes, and liver function
2.5 years	B	Ask about AE and SAE, and about prescription compliance
3 years	A + B	Ask about AE and SAE, and about prescription compliance
3.5 years	B	Ask about AE and SAE, and about prescription compliance
4 years	A + B	Ask about AE and SAE, and about prescription compliance. Order blood tests to measure kidney function, electrolytes, and liver function
4.5 year	B	Ask about AE and SAE, and about prescription compliance
5 years	A + B	End of melatonin treatment. Evaluation of overall survival, metastasis-free survival, and proportion of subjects with metastases^b^. Ask about AE and SAE

A = Follow-ups at St. Erik Eye Hospital or at the participant’s local eye clinic. Examination of the eye, for subjects treated with radiation, or of the prosthesis and/or orbit, for subjects treated with enucleation. Follow-up interval ± 4 weeks during the first year and ± 8 weeks after the first year

B = Radiological examination of the liver with ultrasound or computer tomography every 6 months for the first 5 years after diagnosis; can be performed at the participant’s local healthcare clinic. Follow-up interval ± 4 weeks during the first year and ± 8 weeks after the first year

^a^Primary treatment of uveal melanoma in the eye is either enucleation (surgical removal of the eye) or brachytherapy (local radiation therapy of the eye)

^b^Evaluation of the proportion of subjects with metastases is performed through data collection via registries, chart documentation, and statistical work. It therefore does not require subjects’ active participation

**Table 2 Tab2:** Flowchart

**Time**	**Screening** − 30 days before 1 m visit	**Month 1** ± 7 days	**Month 6** ± 4 weeks	**Year 1** ± 4 weeks	**Year 1.5** ± 8 weeks	**Year 2** ± 8 weeks	**Year 2.5** ± 8 weeks	**Year 3** ± 8 weeks	**Year 3.5** ± 8 weeks	**Year 4** ± 8 weeks	**Year 4.5** ± 8 weeks	**Year 5** ± 8 weeks
Inclusion/exclusion	x											
Informed consent	x											
Randomization melatonin/control group	x											
Medical history, current medication	x											
Medication instruction	x											
Radiological examination—liver			x	x	x	x	x	x	x	x	x	x
Radiological examination—thorax and abdomen	x											
Blood samples	x					x				x		
AE and SAE, prescription compliance		x	x	x	x	x	x	x	x	x	x	x
End of study												x

### Data collection

A case report form (CRF) will be established in paper form and used for data collection, where subjects will be identified through a trial-specific number only. The examiner is responsible for assuring that registered information is correct and complete and that the reporting is performed according to the predetermined timeline. The principal investigator will sign the completed CRF and a copy will be archived where the trial takes place.

### Follow-up

The subjects will take their medication (tablets) at home and confirm that they have received each package of melatonin sent to them. They will, 1 month following recruitment, be contacted via telephone and asked about their compliance to the treatment. The participants will then continue to be contacted via telephone every 6 months throughout the trial period and asked questions about compliance, adverse events (AE), and serious adverse events (SAE). After the termination of the trial, the subjects will continue their yearly control visits at St. Erik Eye Hospital, or at their local ophthalmology clinic, for the remainder of their lives, as all uveal melanoma patients do.

